### Statistics

The primary analysis population is the per-protocol set, consisting of randomized patients with baseline data and data on primary outcome measures, as well as good compliance. This population includes patients who quit the study because of lack of drug effectiveness. The secondary analysis population is the full analysis set according to the intention-to-treat principle; this population includes all randomized patients who receive therapy at least once, regardless of whether they adhere to the protocol or provide a complete dataset. Patients who never receive therapy are excluded. Patients with missing data are included, with adjacent data carried forward to the missing data. The full analysis set population is consistent throughout the entire study. The safety analysis population is the safety set, which includes all patients who receive therapy at least once.

Patient survival rates are analyzed by constructing a Cox regression model that includes multiple variables, such as baseline glomerular filtration rate, severity of disease, age, and treatment group. A non-inferiority test is determined by computing the 95 % confidence interval of the hazard ratio. The same method is used to analyze technique survival rates. Decline in estimated glomerular filtration rate is analyzed by the Wilcoxon rank-sum test. Nutritional status and quality-of-life score are analyzed by analysis of covariance. Rates of cardiovascular events and patient drop-out are analyzed by the Cochran–Mantel–Haenszel *χ*^2^ test. Increments of dialysis dosage from baseline to the end of treatment are analyzed by constructing a mixed model. Medical costs are compared by *t* test or analysis of variance. Adverse events and severe adverse events are categorized according to terminology in the Medical Dictionary for Regulatory Activities. Adverse events, severe adverse events, peritonitis, and allergies are compared by the *χ*^2^ test or Fisher’s exact test. Product quality is evaluated by nonparametric tests.

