In China, the appropriate peritoneal dialysis dosage remains unclear. Western patients are often treated with 8 l/day, whereas 6 l/day is believed sufficient for incident peritoneal dialysis in Asian patients. Chinese patients differ ethnically from patients in Western countries. Although Chinese patients are similar ethnically to patients in Hong Kong and Japan, their economic status, which is important for peritoneal dialysis use, is quite different. Our previous study showed that 6 l/day was sufficient for adequate peritoneal dialysis in Chinese patients, although a 48-week follow-up showed continuous decline in *Kt*/*V* and creatinine clearance rate [20]. Further decreases in *Kt*/*V* and creatinine clearance rate would necessitate increases in peritoneal dialysis dosage. In this study, the observation period is 5 years. Thus, dosage could not be fixed at 6 or 8 l/day; rather, it would have to be changed according to clinical situations. The trial described here would therefore be a study of the effectiveness, not the efficacy, of peritoneal dialysis [42]. The dosage adjustment protocol in this study is almost the same as that in routine clinical circumstances.

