This study compares two types of peritoneal dialysis fluid, one packed in PVC and the other in non-PVC materials. It is known that PVC has deleterious effects on human health, owing to the added plasticizer (i.e., DEHP), although the significance of its toxicity may be exaggerated [43, 44], Moreover, an as-yet-unknown toxicity may manifest during long-term usage. The toxicity of the plasticizer has been confirmed [45, 46], limiting the usage in some countries of PVC materials in medical devices and food and drug utensils [47]. The Chinese National Development and Reform Committee released a catalog of industrial structural adjustments in 2011, although peritoneal dialysis fluids were excluded from the list [48]. However, use of the plasticizer remains a public and medical concern. This is not the first trial to compare PVC and non-PVC materials in peritoneal dialysis, but it is the first long-term head-to-head comparison of peritoneal dialysis fluids packed in PVC and non-PVC materials. Studies have compared the traditional PVC packed dialysis fluid *Dianeal*® and non-PVC packed peritoneal dialysis fluids, but these fluids have many differences other than their packaging, including pH and buffering agent. The two types of peritoneal dialysis fluid in this trial have the same pH, buffer, and osmotic agents, with only the packaging material differing, in that *Dianeal*® is packed in PVC and HUAREN dialysis fluid in non-PVC bags.

This study may also reveal some of the disadvantages of non-PVC material. For example, this material may be stiff and fragile, and may be prone to leakage when used for peritoneal dialysis, resulting in peritonitis. The PVC packaging has better elasticity, flexibility, and durability, making it useful as a liquid container. In a large country, such as China, peritoneal dialysis fluids travel a great distance to reach patients’ homes. Climate, temperature, and physical abrasion all challenge the packaging of dialysis fluids. Transportation of peritoneal dialysis fluids to patients in the far north of China is especially long and difficult and may have deleterious effects if the packaging is not durable. Thus, it remains unclear whether the use of non-PVC packed peritoneal dialysis fluids is feasible in China.

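### The sole primary population for the mortality non-inferiority test is a per-protocol set selected after randomisation, and the full analysis set is not required to agree

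*Protocol article*

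**What the plan says.** The Study design section describes a randomised non-inferiority trial. The Outcomes section makes patient survival at 1 to 5 years primary. The Statistics section analyses survival by Cox regression and judges non-inferiority on the 95 % confidence interval of the hazard ratio.

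The same section fixes the populations:

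- Primary: "The primary analysis population is the per-protocol set, consisting of randomized patients with baseline data and data on primary outcome measures".
- Further condition for membership of that set, with no definition given: "as well as good compliance".
- Retention clause for that set: "This population includes patients who quit the study because of lack of drug effectiveness". No other reason for quitting is mentioned.
- Secondary: "The secondary analysis population is the full analysis set according to the intention-to-treat principle". It takes in treated patients "regardless of whether they adhere to the protocol or provide a complete dataset".
- Missing data in the full analysis set: "Patients with missing data are included, with adjacent data carried forward to the missing data".

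The article gives no rule for the case in which the two sets disagree.

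The Discussion says of the non-PVC material that it "may be prone to leakage when used for peritoneal dialysis, resulting in peritonitis".

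**The concern.** Randomisation makes the arms comparable at entry. A set chosen on later compliance and on having outcome data is no longer the set that was randomised. In dialysis patients followed for years, illness drives both compliance and loss to follow-up, so selection into the set is likely to be related to the risk of death.

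Three features make this matter here.

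- The per-protocol set alone carries the primary claim.
- The condition on outcome data is not needed. A Cox model uses a partly followed patient up to the last date known alive.
- Retention is spelled out for one reason for quitting only. For a patient who leaves after a leak or peritonitis, the text does not say whether the patient, and a later death, stay in the primary comparison. The Discussion itself raises that event as a possible drawback of the test bag.

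At stake is whether a declared non-inferiority on mortality can be trusted at its nominal 2.5 % error rate.

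**Working it through.** The plan attaches no number to its choice of population, so there is no figure of its own to reproduce on this point. Its sample sizes serve below only as arm sizes. (The 310 per group could not be reproduced at the stated one-sided 0.025. That is a separate matter, and nothing here depends on it.)

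**Inputs from the Sample size section.** Baxter 5-year survival 50 %; hazard ratio 1.31; one-sided alpha 0.025; 2 years of recruitment and 5 of observation; 310 per group; 750 enrolled, or 750 / 2 = 375 per group.

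**Assumptions.** 1.31 is the non-inferiority margin and also the true hazard ratio. Survival is exponential. Entry is uniform, so follow-up runs from 5 to 7 years. A net share q of HUAREN deaths is removed by the per-protocol rules. Net means beyond what the loss of follow-up time in both arms accounts for, so that the estimated hazard ratio is multiplied by (1 − q). The documents give no value for q.

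**Step 1, expected deaths.** The hazards are ln 2 / 5 = 0.1386 (Baxter) and 1.31 × 0.1386 = 0.1816 (HUAREN). The probability of death is 1 − [exp(−5λ) − exp(−7λ)] / (2λ).

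- Baxter: 1 − (0.5000 − 0.3789) / 0.2773 = 0.563.
- HUAREN: 1 − (0.4033 − 0.2805) / 0.3632 = 0.662.
- Deaths with 375 per arm: 211.2 and 248.2. With 310 per arm: 174.6 and 205.2.

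**Step 2, false non-inferiority.** P = Φ(−ln(1 − q) / SE − 1.96), with SE = √(1/E_B + 1/[E_H(1 − q)]).

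Worked case, 375 per arm and q = 0.05: SE = √(1/211.2 + 1/235.8) = 0.0947; 0.0513 / 0.0947 − 1.96 = −1.419; P = 7.8 %.

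| Net share of HUAREN deaths lost | Expected HR in the set | P, 310 per arm | P, 375 per arm |
|---|---|---|---|
| 0 | 1.31 | 2.5 % | 2.5 % |
| 2 % | 1.28 | 3.9 % | 4.0 % |
| 5 % | 1.24 | 7.1 % | 7.8 % |
| 10 % | 1.18 | 16.8 % | 19.4 % |
| 20 % | 1.05 | 53.7 % | 61.7 % |

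The 5 % row corresponds to about 10 to 12 deaths. If every patient is followed for exactly 5 years, the 5 % row becomes 6.8 % and 7.4 %, and the 10 % row 15.5 % and 17.8 %.

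**Step 3, direction.** A frailty simulation (4,000 runs, about 20 % excluded, as-randomised hazard ratio about 1.34, so beyond 1.31) compared the false non-inferiority rates in the two sets:

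| Prognosis-related exclusion | Full analysis set | Per-protocol set | Per-protocol HR |
|---|---|---|---|
| Both arms alike | 1.3 % | 1.5 % | 1.35 |
| HUAREN arm only | 1.4 % | 11.4 % | 1.21 |
| Baxter arm only | 1.7 % | 0.2 % | 1.50 |

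Balanced exclusion does little. One-sided exclusion moves the result either way, depending on the arm.

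**The case against.** A per-protocol analysis has a proper place in non-inferiority. Switching and non-adherence can dilute a real difference in the as-randomised set, and that dilution also favours non-inferiority. The plan does include a full analysis set. It also compares drop-out, peritonitis and allergy between the arms, so uneven loss would be visible. All of this stands. It is why the per-protocol set should be kept, and why the fault lies only in its being the sole primary set with no agreement required.

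Several stronger readings are tempting but not supported:

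- A reader might infer that the bias runs towards non-inferiority. Step 3 shows that this needs heavier prognosis-related exclusion in the HUAREN arm. The Discussion says only that the material may leak. All patients receive HUAREN fluid during screening, so some product problems may surface before randomisation.
- A reader might infer that patients who quit for leakage, peritonitis or allergy are excluded. The text names one group that is kept and is silent on the others, and silence is not an exclusion rule.
- A reader might infer that everyone with incomplete follow-up is dropped. Having primary-outcome data need not mean complete 5-year data, and the sample size allows for censoring. The condition is unclear and needless, but it does not plainly say this.
- A reader might infer that a shift in the point estimate from above 1.31 to about 1.20 would yield a false claim. The test uses the confidence interval. With about 422 events, the upper limit is exp(1.96 × 2/√422) = 1.21 times the estimate, so an observed value of about 1.31 / 1.21 = 1.08 or less is needed.
- A reader might take the description of the trial as "therefore be a study of the effectiveness, not the efficacy, of peritoneal dialysis" to contradict the choice of set. In context it explains the flexible dosing, not the analysis population.
- Nothing supports attributing a preferred result to the sponsor. The Discussion describes a use for either outcome.

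The full analysis set as written is only a partial safeguard. It does not bind the conclusion, and its carry-forward sentence is not limited to repeated measures. Applied to survival, carry-forward would treat unknown vital status as alive.

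**Conclusion.** The point holds as a weakness of design, not as a demonstrated bias. The only population that decides a mortality non-inferiority claim is selected on events after randomisation, its rules are explicit for one reason for quitting only, and the as-randomised comparison cannot overturn it. The direction of any bias is unknown.

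The size is conditional. If the net excess loss falls on HUAREN deaths, 5 % of them is enough to raise the error rate roughly threefold (2.5 % to about 7-8 %), and 10 % raises it to about 17-19 %. These figures rest on 1.31 being both the margin and the true hazard ratio, on exponential survival with 5 to 7 years of follow-up, and on loss shares that are assumed. For scale, the plan itself allows for 750 − 620 = 130 patients being lost, but says nothing of how they divide between the arms or how their prognosis compares.

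**What to change.** Change the Statistics section as follows.

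- Make the as-randomised set co-primary: all randomised patients analysed in their allocated group, deaths counted also after the study fluid is stopped, and censoring at the last date known alive in place of carry-forward for survival.
- Declare non-inferiority only if the confidence bound is met in both this set and the per-protocol set.
- Delete the availability of primary-outcome data as a condition of per-protocol membership.
- State how the per-protocol set treats patients who quit for leakage, peritonitis, allergy or other adverse events.

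The cost is mostly wording, with two real burdens. First, vital status must be recorded across 50 centres after patients stop the study fluid. Second, the joint requirement costs power. With 1.31 as the margin, equal hazards and 5 to 7 years of follow-up, 750 patients followed for vital status give about 750 × 0.563 = 422 deaths and 79 % power, by Φ(ln 1.31 × √422 / 2 − 1.96). The 620 evaluable patients give about 349 deaths and 71 %. Joint power is therefore limited by the per-protocol set, at no more than about 71 % on these assumptions.

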### Outcomes

The primary outcome measure is patient survival rates at 1, 2, 3, 4, and 5 years. The secondary outcome measures include peritoneal dialysis technique survival rates of 1, 2, 3, 4, and 5 years; estimated decline in glomerular filtration rate, nutritional status (represented as serum albumin and Subjective Global Assessment Score [25]), quality of life (described by the 36-Item Short-Form Health Survey [26]), cardiovascular events (cardiac sudden death, myocardial infarction, severe arrhythmia, carotid plaque, heart failure, cardiovascular intervention, coronary heart disease without myocardial infarction, stroke or transient ischemic attack, peripheral artery disease), increments of dialysis dosage from baseline to the end, and drop-out rates. Medical costs are also recorded.

Safety evaluations include adverse events and severe adverse events, marked changes of vital signs and laboratory test results, peritonitis (infectious or chemical), allergy to ingredients of peritoneal dialysis fluids and materials of bags and tubing, and quality of dialysis product. Evaluation of product quality includes the transparency of fluid bags, the tightness of connections, and the legibility of labels and texts on packaging.

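### The primary (per-protocol) set conditions on not dropping out, so it is the wrong leading set for the drop-out outcome and a doubtful one for technique survival

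*Protocol article*

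**What the plan says.** The Outcomes section of the protocol article includes among the secondary outcomes "peritoneal dialysis technique survival rates of 1, 2, 3, 4, and 5 years" and, at the end of the list, "increments of dialysis dosage from baseline to the end, and drop-out rates".

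The Statistics section then fixes the populations:

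- The primary population is the per-protocol set, "consisting of randomized patients with baseline data and data on primary outcome measures, as well as good compliance". It adds: "This population includes patients who quit the study because of lack of drug effectiveness".
- The secondary population is the full analysis set: "this population includes all randomized patients who receive therapy at least once, regardless of whether they adhere to the protocol or provide a complete dataset".
- Safety has its own set, made up of all patients treated at least once.

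The same section names the tests. For drop-out: "Rates of cardiovascular events and patient drop-out are analyzed by the Cochran–Mantel–Haenszel" test. For technique survival, following the Cox model for patient survival: "The same method is used to analyze technique survival rates". Neither test is tied to a population of its own.

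**The concern.** A per-protocol set is chosen on what happens after randomisation. For drop-out, that selection is close to the outcome itself. A patient who leaves can fall out of the set in two ways: by being judged not to have complied well, or by lacking data on the primary outcome. The sentence that re-admits those who quit for lack of effectiveness is needed only if quitters are otherwise liable to be left out, and it mentions no other reason for leaving.

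The reasons not mentioned are the ones this trial most needs to see. The Discussion says that the non-PVC bag may be stiff, fragile and prone to leakage leading to peritonitis. A patient who leaves on that account has not left for lack of effectiveness. If such departures are more common on HUAREN, the selection removes more patients from that arm and pulls the two drop-out rates together. In a trial meant to show that HUAREN is not worse, that error runs in the favourable direction.

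**Working it through.** **What the plan gives.** The Sample size section takes 310 per group (620 in total) and enrols 750 for a 20 % drop-out rate, separately from 15 % censoring. The inflation step is 620 × 1.2 = 744, consistent with 750; dividing instead gives 620 / 0.8 = 775. The surplus of 750 − 620 = 130 patients suggests that the sizing treats drop-outs as outside the analysed number. The derivation of the 310 is a separate matter and does not bear on this point. The documents give no figure for how many drop-outs the per-protocol set removes, no breakdown of reasons for leaving and no technique-failure rate. The rest is therefore a range under stated assumptions.

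**Step 1: overall drop-out rate.** Expected drop-outs are 0.20 × 750 = 150, leaving 600 patients. Assume that all 600 stay in the per-protocol set, along with a share *s* of the drop-outs (those who quit for lack of effectiveness). The apparent rate is 150*s* / (600 + 150*s*).

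| *s* (assumed) | drop-outs counted | apparent rate |
|---|---|---|
| 0 % | 0 | 0 % |
| 10 % | 15 | 2.4 % |
| 25 % | 37.5 | 5.9 % |
| 50 % | 75 | 11.1 % |
| 75 % | 112.5 | 15.8 % |
| 100 % | 150 | 20 % |

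The full analysis set would show 20 %, provided all enrolled patients are treated at least once.

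**Step 2: difference between arms.** Assume true drop-out of 15 % on Baxter and 25 % on HUAREN, which averages to the plan's 20 %, with 375 per arm. Among all patients, two-sided 5 %:

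- Standard error under the null: √(2 × 0.20 × 0.80 / 375) = 0.0292.
- Standard error under the alternative: √((0.15 × 0.85 + 0.25 × 0.75) / 375) = 0.0290.
- z = (0.10 − 1.96 × 0.0292) / 0.0290 ≈ 1.47, so power is about 93 %.

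In the per-protocol set, with the same retained share in each arm, each rate becomes *sp* / (1 − (1 − *s*)*p*):

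| *s* | Baxter | HUAREN | gap (points) |
|---|---|---|---|
| 25 % | 0.0375 / 0.8875 = 4.2 % | 0.0625 / 0.8125 = 7.7 % | 3.5 |
| 50 % | 0.075 / 0.925 = 8.1 % | 0.125 / 0.875 = 14.3 % | 6.2 |
| 75 % | 0.1125 / 0.9625 = 11.7 % | 0.1875 / 0.9375 = 20.0 % | 8.3 |

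If the whole excess comes from reasons other than lack of effectiveness (5 % lack of effectiveness in both arms; 10 % other on Baxter, 20 % other on HUAREN), the rates become 5 / 90 = 5.6 % and 5 / 80 = 6.3 %, a gap of 0.7 points.

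The shrinkage is a tendency and not a certainty. If the retained share were 25 % on Baxter and 75 % on HUAREN, the same table gives 4.2 % and 20.0 %, a gap of 15.8 points, wider than the true 10.

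**Step 3: technique survival.** Assume a true 5-year technique survival of 70 %, treated as a simple proportion: 225 failures in 750. If a share *r* of the failures stays in the per-protocol set, apparent survival is 1 − 225*r* / (750 − 225(1 − *r*)). For *r* = 20, 50 and 80 % this gives 92, 82 and 74 %. Nothing in the documents says which *r* applies, and *r* could be close to 100 %.

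**The case against.** The strongest reply is that the plan already contains the right analysis. The full analysis set is planned as the secondary population and keeps every treated patient, adherent or not. On the assumed figures above, it would find the 10-point gap with about 93 % power. Leakage-related harm is also counted elsewhere: peritonitis, allergy to bag materials and product quality are safety evaluations, and safety has its own set. This stands. A reader might infer that drop-outs vanish before anyone counts them, or that a real excess on HUAREN would be reported as no difference. The documents do not support either statement for the trial as a whole.

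Second, the article does not say that every other quitter is excluded. Good compliance is undefined, and a patient who leaves may still have survival data. A reader might also infer that most drop-outs are removed. That needs a retained share below 50 %, and the documents give no reasons for drop-out from which to judge it. This stands too: the share is unknown.

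Third, technique failure is not poor compliance. A patient who follows the protocol and is transferred off peritoneal dialysis can meet all the per-protocol criteria, and failure through inadequate dialysis may count as lack of effectiveness. This makes the technique-survival part clearly the weaker one, and a ban on any per-protocol analysis of it would be a matter of preference.

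Fourth, a condensed article may leave the population for each secondary outcome to the full protocol or SAP. This reply does not succeed. The article is not silent: it fixes one primary population, states the one reason for quitting that is expressly kept, and gives a separate set to safety alone. If the two analyses of drop-out disagree, that hierarchy puts the less interpretable one first.

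**Conclusion.** The point holds for drop-out. As written, the primary comparison of drop-out is made in a set selected partly on not having dropped out, with one reason for leaving expressly exempted. The share of events lost is unknown: from none to all of the 150 expected. When the retained share is equal in both arms, an assumed 10-point difference shrinks to between 3.5 and 8.3 points for retained shares of 25 to 75 %. It shrinks to 0.7 points if the excess lies wholly in reasons that are not re-admitted. Unequal retained shares could distort it in either direction.

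For technique survival the same mechanism is possible, but its size cannot be determined, because it depends on how good compliance is defined and on whether patients who transfer off peritoneal dialysis stay in the set.

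The conclusion rests on reading the single named primary population as applying to these outcomes, since no other is named. It concerns secondary outcomes only and says nothing about the survival test. The loss is confined to the primary analysis, because the full analysis set preserves the events.

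**What to change.** Add one sentence to the Statistics section of the protocol, carried into the SAP: drop-out is analysed in the full analysis set (or in all randomised patients, which also counts those who leave before any treatment) by allocated fluid, with reasons for leaving tabulated by arm; technique survival is analysed primarily in that same set, with the per-protocol result as supportive.

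This changes only which of two planned populations leads for these two outcomes. It needs no new data and no extra patients.

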### Sample size

The sample size is based on both Chinese facilities containing large numbers of patients [27–31] and the Chinese National Renal Data System [32], consisting of smaller units. We have estimated that the mean 5-year survival rate of patients using Baxter dialysis fluid is about 50 %, with a hazard ratio of 1.31. If the recruitment lasts 2 years and the observation 5 years, with *β* = 0.8, a one-sided *α* for the *t* test = 0.025, and 15 % censored data in each group, 310 patients per group will be needed. With a 20 % drop-out rate, 750 patients should be enrolled in this study.

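### Carry-forward of missing values in the full analysis set exempts no endpoint: it freezes declining measures such as GFR and, read literally, counts drop-outs as alive

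*Protocol article*

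**What the plan says.** All references are to the Methods/Design part of the protocol article.

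- **Populations (Statistics).** "The primary analysis population is the per-protocol set, consisting of randomized patients with baseline data and data on primary outcome measures", with good compliance as a further condition. "The secondary analysis population is the full analysis set according to the intention-to-treat principle"; it takes in everyone randomized and treated at least once, whether or not they adhered or have complete data.
- **Missing data (Statistics, within the description of the full analysis set).** "Patients with missing data are included, with adjacent data carried forward to the missing data". No endpoint is named and none is exempted.
- **Survival (Outcomes; Statistics).** "The primary outcome measure is patient survival rates at 1, 2, 3, 4, and 5 years". "Patient survival rates are analyzed by constructing a Cox regression model that includes multiple variables", and "A non-inferiority test is determined by computing the 95 % confidence interval of the hazard ratio". Technique survival is handled the same way.
- **Repeated measures (Statistics).** "Decline in estimated glomerular filtration rate is analyzed by the Wilcoxon rank-sum test". Nutritional status and quality of life are analysed by analysis of covariance.
- **Expected losses (Sample size).** The calculation allows for 15 % censoring in each group and then adds drop-out: with 20 % "drop-out rate, 750 patients should be enrolled in this study".

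**The concern.** This is a stated rule, not a detail left to a later document. Filling a gap with the neighbouring earlier value assumes that nothing changes after the last visit. That is a poor assumption for residual kidney function. The Discussion reports that Kt/V and creatinine clearance were still falling at 48 weeks in the group's previous study, and this trial runs for five years with about half the Baxter patients expected to die and a fifth of patients expected to drop out. A patient who leaves or dies early contributes a small loss, so the arm that loses patients sooner looks better preserved.

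Survival raises a second question. The last recorded vital status of every drop-out is alive. If the sentence is applied to survival, drop-outs are credited with survival to year five when they should leave the risk set at last contact. Two things are then at stake: the survival rates themselves, whose estimation in Chinese patients is a stated aim in the Abstract, and the hazard ratio in the population that serves as a check on the per-protocol result.

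**Working it through.** The article gives no figure for the effect of this rule, so there is none to reproduce. The size is worked out below.

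**Inputs from the Sample size section:** Baxter five-year survival about 50 %; hazard ratio 1.31; drop-out 20 %.

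**Assumptions:** exponential deaths and drop-out, unrelated to each other; 1.31 read as the non-inferiority margin (the article does not label it); drop-out percentages are those over five years in the absence of death; the unequal splits (Baxter/HUAREN) are illustrations; GFR falls linearly with the same true slope in both arms; values are carried past death as well as past drop-out.

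**Rates per year**
- Baxter death rate: ln 2 / 5 = 0.1386. HUAREN at hazard ratio 1.31: 0.1816.
- Drop-out rate: −ln(1 − d)/5, so 15 % → 0.0325, 20 % → 0.0446, 25 % → 0.0575.

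**Repeated measures.** With total loss rate h (death plus drop-out), mean observed time is T = (1 − e^(−5h))/h. Under linear decline the apparent five-year loss is proportional to T, against a true value proportional to 5.

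| Scenario | T Baxter (years) | T HUAREN (years) | Ratio | HUAREN decline looks |
|---|---|---|---|---|
| Hazard ratio 1.31, drop-out 15/25 % | 3.36 (h = 0.171) | 2.92 (h = 0.239) | 0.87 | 13 % smaller |
| Equal mortality, drop-out 15/25 % | 3.36 (h = 0.171) | 3.19 (h = 0.196) | 0.95 | 5 % smaller |
| Hazard ratio 1.31, drop-out 20/20 % | 3.27 (h = 0.183) | 2.99 (h = 0.226) | 0.91 | 9 % smaller |

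The third row shows that a difference in deaths alone distorts the GFR comparison. The direction can reverse. In simulation, with an assumed decline of 1 ml/min per year (true five-year loss 5.0 ml/min) and equal mortality, the apparent losses were:
- 20/20 % drop-out: 3.28 in both arms.
- 10/30 %: 3.45 Baxter, 3.09 HUAREN.
- 30/10 %: 3.10 Baxter, 3.44 HUAREN.

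**Survival level, if drop-outs count as alive.** Recorded deaths by year five = death rate × T. At 20 % drop-out in the Baxter arm: 0.1386 × 3.27 = 0.454, so five-year survival reads as 54.6 % instead of 50 %. If 20 % means the share of patients actually seen to drop out, the drop-out rate is 0.0636 and T = 3.146; recorded deaths are 0.1386 × 3.146 = 0.436 and survival reads as 56.4 %.

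**Hazard ratio, if drop-outs count as alive.** Simulation of 375 per arm (750/2), five years' follow-up, 2,000 runs per scenario, true hazard ratio 1.31; non-inferiority is declared if the upper 95 % limit is below 1.31.

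| Drop-out, Baxter/HUAREN | Apparent hazard ratio | False non-inferiority |
|---|---|---|
| 20/20 % | 1.30 | 2.2 % |
| 15/25 % | 1.22 | 10.2 % |
| 10/30 % | 1.14 | 26.5 % |
| 25/15 % | 1.38 | 0.5 % |
| 30/10 % | 1.49 | 0.1 % |

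A separate run with 310 per arm gave 9.6 % at 15/25 %. A hand check on that row: recorded deaths are 0.1386 × 3.36 = 0.466 and 0.1816 × 2.917 = 0.530, and the ratio of −ln(1 − deaths) is 0.754/0.627 = 1.20, close to the simulated 1.22.

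With drop-outs censored at last contact, the mean hazard ratio is 1.31 to 1.32 (rounded) and false non-inferiority is 1.6 % to 2.6 % in all five patterns, against a nominal 2.5 %.

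**The case against.** The strongest reply concerns survival. The article never says that vital status is carried forward. It analyses survival by a Cox model, which accommodates incomplete follow-up by censoring, and it sizes the trial with 15 % censored data per group. The carry-forward sentence can be read as meant for visit measurements only, and detailed censoring rules are commonly left to a fuller document. This largely stands: counting drop-outs as alive is the literal reading of an unrestricted sentence, not stated text, so the survival results above are conditional.

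A reader might also infer that the rule biases towards non-inferiority whenever drop-out or death differs between the arms. The documents and the arithmetic do not support that. The hazard ratio moves towards non-inferiority only if HUAREN loses more patients; the reverse split works against it, and equal drop-out leaves it near 1.30. A difference in deaths alone does not bias the survival comparison, because deaths are events. GFR decline has no margin and no non-inferiority test, so freezing it distorts a secondary difference test and nothing more. Nor do the documents predict which arm will lose more patients. The Discussion mentions possible stiffness and leakage of non-PVC bags, but also plasticizer toxicity from PVC.

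Finally, the rule is stated for the secondary population, and the per-protocol set requires data on the primary outcome. That also stands, and it limits how serious the point is.

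None of this rescues carry-forward for the repeated measures, where the rule applies on any reading.

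**Conclusion.** The rule is badly fixed and should be changed, but it does not undermine the primary result directly.

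- **Repeated measures:** the defect holds on any reading. Five-year GFR loss is understated, and the between-arm comparison is distorted in either direction when losses differ. The illustrative size is 5 % to 13 % at 15/25 % drop-out, and it depends on the assumed linear decline, the splits and carrying values past death. For albumin, Subjective Global Assessment and SF-36 the mechanism is the same, but the article gives no time course from which to size it.
- **Survival:** conditional on the literal reading. The survival level is overstated by about 5 percentage points at 20 % drop-out. The hazard ratio is essentially unaffected by equal drop-out and biased in either direction by unequal drop-out. The false non-inferiority rate of about 10 % needs 25 % HUAREN against 15 % Baxter drop-out and 1.31 as the margin, neither of which the article states.

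It is also not shown that the full analysis set would err in the same direction as the per-protocol set, so that inference should not be drawn. Grade: should be fixed.

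**What to change.** 1. Delete the carry-forward sentence.
2. State that survival is censored at the last date known alive and technique survival at the last date known to be on the technique. This agrees with the Cox model and with the censoring already assumed in the Sample size section.
3. Analyse GFR, albumin, Subjective Global Assessment and SF-36 by a repeated-measures mixed model on observed data, with the baseline value as covariate and no values imputed after death. This would replace the rank-sum test for GFR and the analysis of covariance for nutrition and quality of life.
4. Optionally, add a sensitivity analysis in which the hazard of HUAREN drop-outs after leaving is raised until the conclusion changes. Censoring keeps the error rate near nominal only if drop-out is unrelated to prognosis, and this would test that.

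The cost is wording and a little more analysis. No new data are needed.
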